## Abstract

**Background:**

Evidence for the role of the gut microbiome in the pathogenesis of non-alcoholic fatty liver disease (NAFLD) is emerging. Strategies to manipulate the gut microbiota towards a healthier community structure are actively being investigated. Based on their ability to favorably modulate the gut microbiota, prebiotics may provide an inexpensive yet effective dietary treatment for NAFLD. Additionally, prebiotics have established benefits for glucose control and potentially weight control, both advantageous in managing fatty liver disease. Our objective is to evaluate the effects of prebiotic supplementation, adjunct to those achieved with diet-induced weight loss, on heptic injury and liver fat, the gut microbiota, inflammation, glucose tolerance, and satiety in patients with NAFLD.

**Methods/design:**

In a double blind, placebo controlled, parallel group study, adults (BMI ≥25) with confirmed NAFLD will be randomized to either a 16 g/d prebiotic supplemented group or isocaloric placebo group for 24 weeks (*n* = 30/group). All participants will receive individualized dietary counseling sessions with a registered dietitian to achieve 10 % weight loss. Primary outcome measures include change in hepatic injury (fibrosis and inflammation) and liver fat. Secondary outcomes include change in body composition, appetite and dietary adherence, glycemic and insulinemic responses and inflammatory cytokines. Mechanisms related to prebiotic-induced changes in gut microbiota (shot-gun sequencing) and their metabolic by-products (volatile organic compounds) and *de novo* lipogenesis (using deuterium incorporation) will also be investigated.

**Discussion:**

There are currently no medications or surgical procedures approved for the treatment of NAFLD and weight loss via lifestyle modification remains the cornerstone of current care recommendations. Given that prebiotics target multiple metabolic impairments associated with NAFLD, investigating their ability to modulate the gut microbiota and hepatic health in patients with NAFLD is warranted.

**Trial registration:**

ClinicalTrials.gov (NCT02568605) Registered 30 September 2015

## Background

Non-alcoholic fatty liver disease (NAFLD) is now the most common cause of chronic liver disease worldwide [1]. NAFLD can progress from simple steatosis to non-alcoholic steatohepatitis (NASH) and finally to cirrhosis and its complications (e.g. hepatocellular carcinoma) [1]. Currently the prevalence of NAFLD is 20-30 % of the general population in affluent countries [2–4]. Since NAFLD is a pathological condition closely associated with obesity and insulin resistance [5], it could be expected that rates will continue to rise in conjunction with the growing severity of obesity [6].

### NAFLD Pathogenesis

In 1998, Day and James [7] proposed a ‘two hit’ hypothesis to describe the pathogenesis of NAFLD whereby insulin resistance [8] contributes to steatosis (first hit), which sensitizes the liver to oxidative stress (second hit) leading to inflammation, fibrosis and necrosis. Additional theories, such as the multiple-hit hypothesis, suggest factors including adipokines and mitochondrial dysfunction may also contribute to NAFLD [9]. Unrestrained free fatty acid flux from adipose tissue has been implicated as a primary contributor to steatosis [10, 11], however recent work has indicated that *de novo* lipogenesis is significantly elevated in NAFLD patients and contributes to both plasma and hepatic fatty acid levels [12–14].

The prevalence of NAFLD is estimated to be as high as 75 % in individuals with obesity, 93 % in individuals with morbid obesity, and 47-87 % in people with type 2 diabetes [1]. From a clinical perspective, it is not the simple steatosis that is of concern, but rather the progression to NASH and fibrosis that carries risk for morbidity and mortality [15]. Among individuals with NAFLD, 10 % will progress to NASH, and a third of those patients with early-stage NASH will progress to cirrhosis within 5–10 years, putting tremendous strain on liver transplant registries [16]. In the United States, there was an 8-fold increase in liver transplants attributed to NAFLD between 2001 and 2009 [17]. Aside from hepatic damage, steatosis may accelerate the progression of dyslipidemia, insulin resistance, and atherosclerosis [18], as well as increase the risk for cardiovascular [19] and kidney disease [20]. Given the increased pressure on already over-burdened health care systems, this patient population represents a group in need of effective treatments. As yet, there is a lack of approved treatments for patients with NAFLD, particularly with fibrosis, and therefore investigation of promising targets, including dietary interventions, are critically needed.

### NAFLD Treatment

Currently there are no medications or surgical procedures approved for the treatment of NAFLD. Several agents have been tested, including vitamin E and the thiazolidinediones class of diabetes medications [21–24], though limitations have been identified with both. In the PIVENS (Pioglitazone, Vitamin E, or Placebo for NASH) trial, vitamin E and pioglitazone both improved hepatic steatosis and lobular inflammation but not fibrosis, and pioglitazone was associated with weight gain (4.8 % increase in body weight) [22, 25]. Rosiglitazone improved steatosis but not any other histologic lesions in patients with NASH, and was also associated with weight gain [21].

Weight loss via lifestyle modification remains the foundation for current clinical management of the disease [26, 27]. A reduction in weight of 3-5 % improves biochemical markers and steatosis in NAFLD patients while 10 % weight loss is required for improvement in inflammation and NASH regression [28, 29]. Still, identification of effective and high impact lifestyle interventions to achieve this degree of weight loss is critically needed to provide evidence-informed recommendations.

### Gut microbiota in NAFLD, obesity and associated co-morbidities

Gut microbiota have emerged as an important environmental factor influencing the pathogenesis of NAFLD [9, 30]. Since the liver and intestine are connected anatomically and via the hepatic portal system, the gut microbiota and their metabolic by-products may influence hepatic pathology. The connection between the gut microbiota and NAFLD is incompletely understood, however, and a recent review only identified four animal and five human studies characterising microbial profiles in NAFLD [31]. In mice fed a high fat diet, *Lactobacillus* positively correlated with the severity of hepatic steatosis and the effect was attributed to the impact of *Lactobacillus* on bile acid metabolism [32]. Supplementing a high-fat diet with *Bifidobacterium pseudocatenulatum* CECT 7765 over seven weeks increased *Bifidobacterium* and decreased Enterobacteriaceae; changes associated with a reduction in hepatic steatosis in conjunction with weight loss and improved insulin sensitivity [33]. Finally, inflammasome-deficient mice displayed a dysbiotic microbiome that exacerbated hepatic steatosis and inflammation [34].

In humans, using experimental dietary choline depletion (known to induce hepatic steatosis), higher baseline levels of Gammaproteobacteria correlated with a lower risk for fatty liver. Conversely, Erysipelotrichi correlated with a higher risk, suggesting a person’s microbiome can impact their susceptibility to fatty liver in response to choline deficiency [35]. Quantification of gut microbiota in NAFLD patients has produced conflicting results [36–38] and differences within phyla highlight the need for deeper sequencing. Furthermore, in many studies the effects of NAFLD were not isolated from those of simple obesity. From a treatment perspective, administration of a probiotic combination increased Bacteroidetes and decreased Firmicutes after six months, which correlated with reduced hepatic fat [39]. Further, a meta-analysis evaluating probiotic treatment in NAFLD, found reduced liver enzymes (ALT, AST), TNF-α, total cholesterol and insulin resistance, suggesting that altering gut microbiota may beneficially affect NAFLD [40].

Changes in the gut microbial environment in obesity and type 2 diabetes have been well-documented. These conditions, which are closely tied to NAFLD development, are known to be associated with changes in the vast and diverse communities of microorganisms that live in the human intestinal tract [41–44]. Although not unanimously shown, obesity is associated with a phylum-wide increase in Firmicutes and a reduction in Bacteroidetes [42, 45–47]. This shift is believed to enhance energy harvest, thereby promoting weight gain, hyperglycemia and insulinemia [43, 48–50]. The microbiota also affect the integrity of the gut barrier; in the case of obesity and high fat diets, changes in gut integrity translate to increased intestinal permeability and translocation of endotoxin (lipopolysaccharide from Gram-negative bacteria) [9, 51–53]. Increased leakage of endotoxin into the bloodstream is called metabolic endotoxemia and has been linked to the onset of metabolic diseases [52]. In NAFLD patients, endotoxin levels are elevated [54, 55] and have been associated with small intestinal bacterial overgrowth [9, 56, 57]. The microbiota can also produce endogenous ethanol [9] and ~300 other volatile organic compounds (VOC) [58], some of which may contribute to liver injury. Recently, it has been shown that obese NAFLD patients have an altered microbiome and unique fecal VOC profile compared to healthy controls [38]. While the effect of VOC on liver function is unknown, it is plausible that excess VOC may contribute to a state of elevated inflammation and hepatocyte stress. Given the profound metabolic impact of the gut microbiota to the host, therapeutic manipulation of this community may aid in treatment of NAFLD.

### Prebiotics

Prebiotics are nondigestible food ingredients that are fermented in the gut and modulate the microbiota in a manner beneficial to the host [59–61]. Prebiotic fiber is found naturally in common foods such as asparagus, garlic, leeks and onions [62]. The average intake of prebiotic fiber is estimated to be 1-4 g/d in the Unites States and 3-11 g/d in Europe [63].

There are numerous animal and human studies that point to the potential of prebiotics to treat NAFLD [60, 64–67]. Our lab and others have consistently shown that prebiotic supplementation is associated with lower body weight and/or reduced weight gain in normal [68], genetically obese [69] and high fat, high sucrose-fed [70, 71] rats. We were also the first to report that prebiotic supplementation improves weight loss and reduces energy intake in overweight and obese adults compared to placebo [72], which has since been shown in patients with type 2 diabetes [73]. Increases in satiety hormones observed with prebiotics, including glucagon-like peptide-1 (GLP-1) and peptide YY (PYY) and decreases in the orexigenic hormone ghrelin, likely mediate some of the reduced *ad libitum* energy intake contributing to weight loss [68, 70–72, 74, 75]. These modifications observed with prebiotic supplementation are notable because greater satiety and lower hunger are associated with improved adherence to weight loss interventions [76–79]. Further, the metabolic benefits of prebiotics were evaluated in a recent systematic review of 26 randomized controlled trials [80], where prebiotics were shown to improve satiety, postprandial glucose and insulin in both healthy and obese individuals.

Prebiotics alter gut microbiota in favor of host health [63], including modifying gut barrier integrity and endotoxin translocation. For example, prebiotics increase *Bifidobacterium* which is correlated with lower serum endotoxin levels [81]. In addition, prebiotics stimulate the gut trophic hormone glucagon-like peptide-2, which can modulate endotoxin translocation via effects on epithelial tight junctions [53]. Steatosis itself increases the vulnerability of the liver to injury from endotoxin; while other NAFLD treatment such as vitamin E and thiazolidinediones may reduce steatosis, there is no human evidence that currently suggests vitamin E or the glitazones attenuate endotoxin levels.

The NAFLD Activity Score (NAS) is a histologically-based tool used to grade steatosis, lobular inflammation and ballooning in patients with NAFLD. While weight loss has been shown to reduce NAS, this is largely driven by reductions in steatosis but not ballooning or inflammation, and it does not appear to affect fibrosis [82]. By contrast, we have preliminary histopathological evidence from a pilot trial suggesting that prebiotic fiber improves several hepatic outcomes (i.e. fibrosis) that would augment improvements from weight loss alone (i.e. steatosis) (Unpublished observations; [name], [name]). This finding is supported by a recent report that 24 weeks of prebiotic (fructooligosaccharide) plus probiotic (*Bifidobacterium longum*) reduced serum AST, endotoxin and hepatic steatosis in NASH patients [83]. Our recent review [61] highlights convincing evidence from animal and human studies for the potential of prebiotics as a multi-target strategy to treat NAFLD. It is our hypothesis that prebiotic supplementation, as an adjunct to lifestyle-mediated weight loss, will improve hepatic and metabolic pathways beyond those targeted by weight loss alone.

### Specific objectives

The primary objective of this study is to determine the efficacy of a prebiotic supplement in combination with registered dietitian supported weight loss in reducing hepatic injury and liver fat in NAFLD patients over 6 months. Secondary objectives include determining the effect of prebiotic supplementation plus weight loss on appetite, body composition, glucose tolerance, inflammatory cytokines, and potential mechanisms related to gut microbiota, volatile organic compounds, and *de novo* lipogenesis. The research study is novel in that it has been designed to provide comprehensive information on liver health outcomes in NAFLD patients in conjunction with a mechanistic investigation into several of the “multi-hits” thought to promote NAFLD and its progression to NASH.

Given the primary objective of determining the impact of prebiotics on hepatic injury and liver fat in NAFLD patients from baseline to 6 months, patients will undergo a liver MRI, a FibroScan and blood FibroTest. Changes in gut microbiota, VOCs, and LPS will elucidate the effects of prebiotic modulation of the gut microbiota and their metabolic by-products. The impact of prebiotics on obesity-related outcomes will be evaluated through anthropometrics, subjective appetite ratings and satiety hormone responses. Insulin resistance is also closely associated with NAFLD and the effects of prebiotics on glucose regulation will be assessed via responses to an oral glucose challenge. Inflammatory cytokines are another potential “hit” and the effect of prebiotics on plasma inflammatory markers will be quantified. Finally, there is potential for prebiotics to reduce lipogenesis due to its effects on glucose tolerance, food intake, and gut microbiota, and this will be investigated via measurement of *de novo* lipogenesis. This trial is designed to test whether prebiotic supplementation augments the reduction in steatosis attributed to weight loss alone. We hypothesize that the addition of a prebiotic supplement to a registered dietitian-led weight loss intervention, will improve hepatic injury and steatosis to a greater extent than weight loss alone.

## Methods/design

### Ethics, consent and permission

This proposal has been approved (REB14-2464) by the Conjoint Health Research Ethics Board of the University of Calgary (Calgary, AB, Canada). Voluntary, written, informed consent will be obtained from each participant.

### Design

The study is a single-center double blind, placebo controlled, parallel group study. Patients will be randomized to a 16 g/d prebiotic supplemented group or isocaloric placebo group for 24 weeks. All participants will receive individualized dietary counseling sessions with a registered dietitian to achieve 10 % weight loss.

### Inclusion criteria

Adult participants (aged 18–65, BMI ≥25 kg/m^2^) diagnosed with NAFLD on the basis of abnormal liver enzymes (ALT > 1.5x upper limit of normal) and ultrasonography [84] will be recruited from the South Health Campus Fatty Liver Clinic and the surrounding community in Calgary, Alberta, Canada. Individuals with type 2 diabetes treated with diet and exercise alone or metformin will be included, as well as individuals with aspartate aminotransferase and alanine aminotransferase ≤10x upper limit of normal.

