### Exclusion criteria

Exclusion criteria include other causes of liver disease such as viral hepatitis and alcoholic liver disease; cirrhosis of the liver (FibroScan >17.5kPa or FibroTest >0.8) or clinical features of cirrhosis; alcohol consumption >20 g/day (2 standard drinks) in women or > 30 g/d (3 drinks) in men; alternate (e.g. TPN) or concomitant etiology for abnormal liver enzymes; history of decompensated liver disease including ascites, encephalopathy or variceal bleeding; concomitant use of any weight loss medication or herbal weight loss products, previous bariatric or other intestinal surgery known to affect food intake or digestive function; presence of active infection, pregnancy or lactation; regular use of a probiotic or prebiotic supplement within 3 months prior to enrollment; antibiotic use within 3 months prior to enrollment; weight loss >3 kg within the preceding 3 months to enrollment; uncontrolled cardiovascular or respiratory disease, active malignancy, or chronic infections; use of agents such as vitamin E, omega-3 fatty acids or medications with evidence for effects on NAFLD (pioglitazone, GLP-1 analogues, dipeptidyl peptidase IV inhibitors, ursodeoxycholic acid); and patients with type 2 diabetes where HbA1c is >9 %.

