### Randomization

Participants will be randomized in equal numbers to two groups, stratified by sex, BMI, and age for allocation into prebiotic or placebo arms. Randomization sequences will be prepared by an independent statistician and entered into a web-based central randomization program. Sequences will not be revealed to investigators or study staff. Randomization will be in blocks of 4 within each sex/age/BMI stratum. To maintain blinding of the trial coordinator and registered dietitian, a research assistant with no involvement in the study will use the central randomization program at the randomization visit. Study personnel will be unaware of treatment allocation prior to the assignment of interventions, using sequentially numbered, opaque, sealed envelopes to maintain allocation concealment. The clinical trial coordinator will enroll participants. Participants, research staff and outcome assessors will be blinded to participants’ assigned group. Participants will receive the prebiotic or placebo supplement in identical foil packets to maintain blinding. An overview of the study design and measurement outcomes is presented in Fig. 1.

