### Statistical analyses

Statistical analyses will be performed using SPSS 22.0 software (IBM, Armonk, NY). Values with skewed distribution will be logarithmically transformed prior to analysis. Baseline characteristics will be compared between groups using chi-square for categorical variables and t-tests for continuous variables. Primary analysis will be performed on an intent-to-treat basis, regardless of subject compliance. The primary outcome measures are change from baseline to 24 weeks in hepatic injury (Fibrotest, FibroScan) and liver fat (percent measured by MRI). ANCOVA, with testing for confounding factors (sex) and potential covariates (BMI, age and fasting insulin) will be used to assess the difference between groups at weeks 0 and 24. Should the main effect of diet be significant, Tukey’s multiple comparison test will be used. Secondary outcomes measured at 0 to 24 weeks (e.g. satiety hormones, body fat, glycemia and insulinemia) will be analyzed with ANCOVA as above. For variables measured over time (e.g. body weight, satiety hormones and glucose at 0, 30, 60, 120 and 180 minutes), a mixed model of repeated measures ANCOVA will be applied to examine the effect of treatment, time and their interaction. Our planned secondary analysis will be per protocol with all participants who complete the 24 week intervention and are compliant based on consumption of ≥80 % the product doses. Cases with missing outcome data will be excluded from analysis. Results will be considered statistically significant (2-sided) at *P* ≤ 0.025 (Bonferroni adjustment for 2 primary outcomes).

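### Glycaemic and insulin secondary outcomes: adding diabetes status and the outcome's own baseline value as fixed covariates would recover some precision at almost no cost

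*Protocol article*

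**What the plan says.** Under Inclusion criteria, the protocol article states: "Individuals with type 2 diabetes treated with diet and exercise alone or metformin will be included". People without diabetes are eligible too. The Exclusion criteria set an upper limit by removing "patients with type 2 diabetes where HbA1c is >9"%, and also rule out several drugs, among them pioglitazone, GLP-1 analogues and DPP-IV inhibitors.

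Under Randomization, allocation is "stratified by sex, BMI, and age for allocation into prebiotic or placebo arms", and "Randomization will be in blocks of 4 within each sex/age/BMI stratum".

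Under Statistical analyses, the adjustment set for the primary outcomes is named: "ANCOVA, with testing for confounding factors (sex) and potential covariates (BMI, age and fasting insulin) will be used". The same model is then extended: "Secondary outcomes measured at 0 to 24 weeks (e.g. satiety hormones, body fat, glycemia and insulinemia) will be analyzed with ANCOVA as above". For OGTT glucose over the sampling times, "a mixed model of repeated measures ANCOVA will be applied to examine the effect of treatment, time and their interaction". Neither diabetes status nor the outcome's own baseline value is named as a covariate in either model.

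**The concern.** Glucose tolerance is a stated secondary objective, and glycaemic and insulinaemic responses are named secondary outcomes in the abstract. Whether a participant has treated type 2 diabetes is likely to be one of the stronger predictors of these measurements, and it must be known at screening to apply the entry criteria. The plan gives an explicit list of adjusters for these outcomes and leaves this one out. Fasting insulin and BMI will pick up part of the difference, but neither identifies who has diabetes or who takes metformin.

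Whatever the listed covariates do not explain stays in the error term. With about 24-25 evaluable participants per arm, that widens the confidence interval for the glucose and insulin comparisons. The stake is efficiency on a secondary objective.

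**Working it through.** **The plan's own figures.** The sample size section covers only the liver outcomes, so there is no glycaemic figure to reproduce. The liver figures do reproduce with n = 2[(z₁ + z₂)·SD/Δ]², z₁ = 2.241 (two-sided 0.025), z₂ = 0.842 (80% power):

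- MRI fat: 2(3.083 × 5.0/4.4)² = 24.5, so 25.
- FibroScan: 2(3.083 × 4.0/4.1)² = 18.1, so 19.
- FibroTest: 2(3.083 × 0.056/0.08)² = 9.3, so 10.

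**Inputs for the check**

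- Evaluable per arm: 30 × 0.80 = 24 (stated recruitment and dropout).
- Significance level: 0.025 two-sided, from "Results will be considered statistically significant (2-sided) at *P* ≤ 0.025 (Bonferroni adjustment for 2 primary outcomes").
- Share with diabetes, p: not in the documents; assumed 0.20-0.40. The 47-87% in the Background is the prevalence of NAFLD among people with diabetes, so it cannot be used here.
- Separation, d, between people with and without diabetes, in within-group SD: not in the documents; assumed 0.5-1.0 for change from baseline and 1-2 for levels.
- Within-group correlation, ρ, of baseline with week 24: not in the documents; assumed 0.5-0.7.
- Reference effect: 1.0 residual SD of the model that includes diabetes status. By the noncentral t with 24 per arm, power is 87%. The degree of freedom spent on the covariate is ignored.

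**Change score, status left out.** Variance inflation = 1 + p(1−p)d².

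| p | d | Inflation | Power |
|---|---|---|---|
| 0.2 | 0.5 | 1 + 0.16 × 0.25 = 1.04 | 86% |
| 0.4 | 0.5 | 1 + 0.24 × 0.25 = 1.06 | 85% |
| 0.2 | 1.0 | 1 + 0.16 × 1 = 1.16 | 81% |
| 0.4 | 1.0 | 1 + 0.24 × 1 = 1.24 | 78% |

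**Own baseline in the model, status left out.** Let B = p(1−p)d² and T = 1 + B, with the same d at baseline and week 24. Inflation = [T − (B + ρ)²/T]/(1 − ρ²).

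- Smallest (p = 0.2, d = 1, ρ = 0.7): B = 0.16, T = 1.16; [1.16 − 0.86²/1.16]/0.51 = 1.02; power 86%.
- Largest (p = 0.4, d = 2, ρ = 0.5): B = 0.96, T = 1.96; [1.96 − 1.46²/1.96]/0.75 = 1.16; power 81%.

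**Is chance imbalance an additional harm?** The arm difference in diabetes share has SD √(2p(1−p)/24), which is 0.12 at p = 0.2 and 0.14 at p = 0.4. It moves the treatment difference by d times that amount, a variance of d²·2p(1−p)/24. The variance that status adds to the arm difference when it is left in the error term is (2/24)·p(1−p)d². These are the same quantity: with p = 0.4 and d = 1, both equal 0.020. The ordinary standard error already contains it.

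**Weak association.** With d = 0.25 on change, p(1−p)d² is 0.010-0.015, and adjusting for status cuts the standard error by less than 1%.

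**The case against.** The strongest reply is that nothing here is an error. Randomisation keeps the comparison unbiased and the type I error rate controlled without this covariate, the outcomes are secondary, and every input that drives the size is assumed. Fasting insulin, BMI, the HbA1c limit and the drug exclusions already narrow the spread. All of that stands, and it limits the point to an efficiency gain. It does not remove the point: the article names its adjustment set and applies it to glycaemia and insulinaemia, so the choice has been made and not merely left open.

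Three stronger readings are tempting but are not supported.

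- **Power could fall to 57%.** This requires raw week-24 levels with no use of baseline, d = 2 and 40% with diabetes, all together (inflation 1 + 0.24 × 4 = 1.96). The abstract frames the secondary outcomes as change, and the analysis section defines the primary measures as change from baseline before applying the same ANCOVA to secondary outcomes. That section's reference to group differences at weeks 0 and 24 is loose enough that a levels analysis cannot be excluded, but it is the less natural reading.
- **Chance imbalance is a second problem on top of noise.** The working shows that they are one variance, which should be counted once.
- **Diabetes should have been a stratification factor.** With 60 participants, three factors and blocks of 4, leaving it out is not a defect. If each factor had two levels (an assumption), a fourth would give 16 strata averaging 60/16 = 3.75 participants, fewer than one block.

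**Conclusion.** The point holds as a nearly free improvement for secondary outcomes only. The glycaemic and insulin comparisons are valid on average as planned but give up some precision. The size cannot be derived from the documents. With an assumed 20-40% diabetes share, the avoidable variance is about 4-24% for a change score, or about 2-16% if the outcome's own baseline is adjusted for. In power terms, 87% becomes about 86-78% in the first case and 86-81% in the second. With a weak association the gain is negligible. The primary liver outcomes are not claimed to be affected.

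**What to change.** In the Statistical analyses section, state that the ANCOVA and mixed models for HbA1c, OGTT glucose and insulin, HOMA and QUICKI include two fixed, pre-specified covariates: diabetes status at screening (yes/no) and the baseline value of the outcome being analysed. State also that both stay in the model whatever imbalance is observed, so that the adjustment does not depend on the baseline tests or on covariate testing. The baseline value belongs in the same sentence because, once it is in, only 2-16% of variance is left for status to recover under the assumptions above.

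The randomisation strata need not change. The cost is one line of text and one or two degrees of freedom out of about 48 participants. Diabetes status is already needed for eligibility and the baseline values are already measured, so no new data are collected.
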